## Abstract

**Background:**

Atypical meningiomas are an intermediate grade brain tumour with a recurrence rate of 39–58 %. It is not known whether early adjuvant radiotherapy reduces the risk of tumour recurrence and whether the potential side-effects are justified. An alternative management strategy is to perform active monitoring with magnetic resonance imaging (MRI) and to treat at recurrence. There are no randomised controlled trials comparing these two approaches.

**Methods/Design:**

A total of 190 patients will be recruited from neurosurgical/neuro-oncology centres across the United Kingdom, Ireland and mainland Europe. Adult patients undergoing gross total resection of intracranial atypical meningioma are eligible. Patients with multiple meningioma, optic nerve sheath meningioma, previous intracranial tumour, previous cranial radiotherapy and neurofibromatosis will be excluded. Informed consent will be obtained from patients. This is a two-stage trial (both stages will run in parallel):

Stage 1 (qualitative study) is designed to maximise patient and clinician acceptability, thereby optimising recruitment and retention. Patients wishing to continue will proceed to randomisation.

Stage 2 (randomisation) patients will be randomised to receive either early adjuvant radiotherapy for 6 weeks (60 Gy in 30 fractions) or active monitoring.

The primary outcome measure is time to MRI evidence of tumour recurrence (progression-free survival (PFS)). Secondary outcome measures include assessing the toxicity of the radiotherapy, the quality of life, neurocognitive function, time to second line treatment, time to death (overall survival (OS)) and incremental cost per quality-adjusted life year (QALY) gained.

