### Inclusion criteria

For inclusion, each patient must meet the following criteria:Histologically confirmed newly diagnosed solitary atypical meningioma (WHO grade II) based on the 2007 WHO criteria [1]Age ≥ 16 yearsAll anatomical locations allowed except optic nerve sheath tumourComplete resection (Simpson 1, 2 or 3) as assessed by the surgeonAble to commence radiotherapy between within 12 weeks of surgery (ideally 8 to 12 weeks)WHO performance status 0, 1 or 2Women of reproductive potential must use effective contraception for the whole duration of the treatmentAbsence of any psychological, familial, sociological or geographical condition potentially hampering compliance with the study protocol and follow-up schedule; those conditions should be discussed with the patient before registration in the trial.

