### Exclusion criteria

Patients exhibiting any of the following will be excluded from the study:Neurofibromatosis type II (NF-2)Optic nerve sheath tumoursMultiple meningiomasRadiation induced meningiomaClinical evidence of second malignancies, except a history of cervix carcinoma in situ and/or basal cell carcinomaPrevious intracranial tumourPregnant or lactating women.

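### The Abstract excludes previous cranial radiotherapy, but the article's formal eligibility criteria contain no such exclusion

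*Protocol article*

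**What the plan says.** The protocol article states its exclusions twice.

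The Abstract, under Methods/Design, names five: multiple meningioma, optic nerve sheath meningioma and then "previous intracranial tumour, previous cranial radiotherapy and neurofibromatosis will be excluded".

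The Exclusion criteria section gives the formal list. Most of it reads, as extracted, "Neurofibromatosis type II (NF-2)Optic nerve sheath tumoursMultiple meningiomasRadiation induced meningiomaClinical evidence of second malignancies". Two exceptions to the second-malignancy item follow, then previous intracranial tumour, and pregnancy or lactation. Previous cranial radiotherapy is not among the items.

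The Inclusion criteria require a tumour described as "Histologically confirmed newly diagnosed solitary atypical meningioma (WHO grade II" and add conditions on age, location, completeness of resection, timing of radiotherapy, performance status, contraception and ability to comply. None concerns earlier irradiation. The Study population section opens the trial to adults with atypical meningioma who satisfy the eligibility criteria, so the wording of those criteria defines who may enter.

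**The concern.** The two statements do not define the same population. An abstract normally shortens a list by dropping items. This one names a criterion that the list it summarises does not contain.

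Earlier cranial radiotherapy is not a neutral characteristic here. The intervention is 60 Gy in 30 fractions (Abstract; Stage 2). The Background names neurocognitive impairment, hypopituitarism and radiation-induced tumours among the risks of radiotherapy, and the Secondary endpoints include toxicity and neurocognitive function. Whether previously irradiated patients may enter therefore bears on the safety of individual participants and on how those two endpoints are read. It also matters to anyone who needs to know to which patients the results apply.

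**Working it through.** No figure is involved and no arithmetic applies. The check is an item-by-item comparison.

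| Exclusion in the Abstract | Counterpart in the Exclusion criteria | Result |
|---|---|---|
| Multiple meningioma | Multiple meningiomas | Match |
| Optic nerve sheath meningioma | Optic nerve sheath tumours | Match |
| Previous intracranial tumour | Previous intracranial tumour | Match |
| Neurofibromatosis, no type given | "Neurofibromatosis type II (NF-2") | Narrower in the formal list |
| Previous cranial radiotherapy | None; nearest item is radiation-induced meningioma | Absent |

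Three of the five match, one is narrower and one is absent. The formal list also holds three items that the Abstract does not mention: radiation-induced meningioma, second malignancies, and pregnancy or lactation. Those three are ordinary condensation and are not part of this point.

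**Could another criterion stand in for the absent one?** Each candidate was tried in turn.

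1. Radiation-induced meningioma concerns what caused the present tumour. Previous cranial radiotherapy concerns what the patient has been exposed to. A patient irradiated earlier whose meningioma is not attributed to that exposure does not meet this exclusion.
2. Previous intracranial tumour removes those whose earlier radiotherapy was given for such a tumour. It does not reach cranial radiotherapy given for another reason.
3. Clinical evidence of second malignancies removes a further group, subject to its two exceptions. It does not reach a patient with no such evidence.
4. The inclusion requirement of a newly diagnosed, solitary tumour describes the meningioma and says nothing about earlier treatment of the head.

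**What remains.** Take a patient with earlier cranial radiotherapy, no previous intracranial tumour, no clinical evidence of a second malignancy, and a meningioma not judged radiation-induced. That patient meets no exclusion in the formal list, yet is excluded by the Abstract. Items 1 to 3 make this group small but do not empty it. The article gives no figure from which its size could be estimated.

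**Neurofibromatosis.** Read literally, a patient with neurofibromatosis other than type II is excluded only by the Abstract. The general word may well be shorthand for the specific diagnosis, so this is a point of wording.

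**The case against.** The strongest reply is that this is a journal article condensing a fuller protocol. Nothing in it says that sites judge eligibility from the article, still less from its abstract. The full protocol and the eligibility checklist may already treat previous cranial radiotherapy consistently. The formal list also does not claim to be exhaustive.

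This stands against the stronger conclusion that a reader might draw, namely that the trial will admit previously irradiated patients to a 60 Gy arm. The article cannot show that. Nor does anything suggest that someone chose to admit them, so this is an inconsistency of wording and not a flaw in the design. The reply does not remove the inconsistency. The formal list is detailed enough to carry named exceptions to one of its items, and the Abstract still contains a criterion that the list lacks. Condensation does not explain an addition.

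A second reply is that other exclusions already catch most such patients. This also stands: the gap is narrow, though not closed.

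A third concerns size. A reader might infer that a few late-toxicity cases among such patients would distort the results. The article does not support this. It does not say how many candidates have had earlier cranial radiotherapy, and under 1:1 randomisation such patients would be expected in both arms, so bias in the comparison is not shown. No effect on the primary endpoint, power or type I error follows either.

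Finally, it is fair to say that the neurofibromatosis difference is probably a general term set beside a specific one, and that no safety or analytic consequence has been shown for it. It is kept only as a minor note.

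**Conclusion.** The inconsistency is real. The Abstract and the formal criteria give different answers on previous cranial radiotherapy, and both cannot be right. The affected group is the narrow one set out in the comparison.

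The conclusion rests on reading the article's criteria as written. It does not assume that the full protocol shares the gap, and it claims neither that such a patient has been or will be randomised nor that any estimate would be biased.

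The point still deserves correction. It touches individual safety in a trial of 60 Gy and the interpretation of the toxicity and neurocognitive endpoints, and it leaves the published population ambiguous. Which of the two rules is right is a clinical decision and is not judged here.

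**What to change.** Reconcile the exclusions in the Abstract with the Exclusion criteria section so that the article carries one list. The clinical leads should decide each item that differs, previous cranial radiotherapy first. Then confirm that the full protocol and the eligibility checklist used before randomisation agree with that list. At the same time, use one term for neurofibromatosis in both places.

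The cost is a wording correction and one check of the checklist. Given how narrow the gap is, the effect on recruitment should be negligible whichever way the item is decided, although the article gives no count to confirm this. The sample size and the planned analyses are unaffected.

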**Discussion:**

ROAM/EORTC-1308 is the first multi-centre randomised controlled trial designed to determine whether early adjuvant radiotherapy reduces the risk of tumour recurrence following complete surgical resection of atypical meningioma. The results of this study will be used to inform current neurosurgery and neuro-oncology practice worldwide.

**Trial registration:**

ISRCTN71502099 on 19 May 2014.

## Background

Meningiomas arise from the linings of the brain, account for 25 to 33 % of adult primary brain tumours and have a peak incidence at age 40 to 60 years [1]. The World Health Organisation (WHO) [1] classifies three grades:Benign (grade I) meningioma (approximately 90 %)Atypical (grade II) meningioma (approximately 7 %)Anaplastic (grade III) meningioma (approximately 3 %)

**Fig. 1 Fig1:**
[figure not shown]
ROAM/EORTC 1308 study design

The annual UK incidence of atypical meningioma is estimated at 0.2 to 0.5/100,000 per year and approximately 150 undergo surgical resection each year. Since the publication of the 2000 WHO classification, the reported incidence of atypical meningioma has risen to 20 to 35 % [2–4]; nevertheless, they remain uncommon. The primary treatment for symptomatic or enlarging atypical meningioma is surgical excision, and the completeness of the resection is an important prognostic factor [5]. Simpson defined the extent of resection into five categories [5]:Simpson 1: complete tumour removal, including dural attachment and any abnormal boneSimpson 2: complete tumour removal, with coagulation of dural attachmentSimpson 3: complete tumour removal, without resection or coagulation of its dural attachmentSimpson 4: partial tumour removalSimpson 5: biopsy only

In modern neurosurgery Simpson 1–3 constitute gross total resection (GTR), and Simpson 4–5 constitutes subtotal resection (STR).

Benign (grade I) meningiomas have a low risk of recurrence (approximately 10 % at 5 years) following surgical resection and are managed by active monitoring with magnetic resonance imaging (MRI) scans. For anaplastic (grade III) meningioma, adjuvant radiotherapy is indicated following surgery to prolong time to recurrence; however, the 5-year progression-free survival is only approximately 10 % [6]. In atypical meningioma (grade II), the 5-year tumour recurrence rates are reported as between 39 and 58 %, and in those patients with residual solid tumour, radiotherapy is administered to reduce the risk of recurrence. However, in patients with gross total resection the role of early adjuvant radiotherapy has not been defined, and the options of radiotherapy or active monitoring are discussed with individual patients. Whilst radiotherapy has been shown to be an effective adjuvant treatment in some studies [7, 8] but not others [2, 9, 10], no consensus exists as to which of these approaches is best. A recently published systematic review concluded that since atypical meningioma preferentially recur within 5 years, future studies should investigate the role of early adjuvant radiotherapy in these patients [11]. There have been no randomised controlled trials in this tumour population. Currently, the treatment decision for adjuvant radiotherapy varies according to the patient, surgeon and neuro-oncologist preference [12, 13], and some European expert opinion recommends that all atypical meningioma patients should have radiotherapy (http://meningiomauk.org/radiotherapy/). No agreement exists on the current standard of care for patients with atypical meningioma undergoing complete resection. Whilst the use of radiotherapy may obviate the need for further surgical procedures, this must be balanced against the potential risks of radiotherapy (from 3.4 to 16.7 % [11]), which include neurocognitive impairment, hypopituitarism and radiation-induced tumours. Equally, tumour recurrence can also affect neurocognitive function (NCF) and quality of life (QoL). Tumours that recur can be treated with further surgery and radiotherapy.

ROAM/EORTC-1308 (Radiotherapy versus Observation following surgical resection of Atypical Meningioma) was funded to determine whether early adjuvant radiotherapy reduces tumour recurrence compared to active monitoring in patients with newly diagnosed atypical meningioma who have undergone gross total resection.

### Primary objective

The primary objective of the study was to determine whether early adjuvant fractionated radiotherapy reduces the risk of tumour recurrence compared to active monitoring in newly diagnosed atypical meningioma.

### Secondary objectives

The secondary objectives were as follows:To assess the early and late effects of fractionated radiotherapyTo assess and compare quality of life in patients with atypical meningioma according to the treatment armTo assess and compare the neurocognitive function in patients with atypical meningioma according to treatment armTo record the second-line treatments (surgery, radiotherapy, and radiosurgery) used at tumour recurrence according to the treatment armTo determine the overall survival (OS) at 5 yearsTo assess the cost-effectiveness of adjuvant radiotherapy compared to active monitoring (UK sites only)To correlate proliferation rate and molecular characteristics with time to tumour recurrence (separate research funding will be sought).

## Methods/Design

### Design overview

ROAM/EORTC-1308 is an international, multi-centre, phase III, randomized controlled trial comparing early adjuvant radiotherapy (intervention) with observation (comparator) in patients who have undergone gross total resection of an intracranial atypical meningioma. This is a two-stage trial, and both stages will run in parallel:

#### Stage 1 (qualitative study)

The stage is designed to maximize patient and clinician acceptability, thereby optimizing recruitment and retention. Patient permission will be sought to allow audio-recording of the consultations during which patients are approached for recruitment to the trial. The qualitative study will examine how information about the trial is exchanged by clinicians and patients as they discuss ROAM and consent is sought. As well as audio-recording the recruitment consultations, a qualitative researcher will subsequently interview a sub-sample of patients and clinicians. The qualitative study will draw on previously described methods [14–16] to identify the source of any recruitment difficulties and design bespoke strategies to optimise recruitment. This approach has demonstrated success in enhancing recruitment in previous trials [17] and aims to improve the patient experience by improving information exchange and communication. Specifically, the qualitative study will compare discussions during recruitment consultations, with clinicians’ and patients’ interpretations of these consultations.

#### Stage 2 (randomization)

In stage 2, patients will be randomized in a 1:1 ratio to early adjuvant radiotherapy (60 Gy in 30 fractions) for 6 weeks (intervention) or active monitoring with MRI (comparator).

### Research setting

The trial will be conducted across 20 adult regional neurosurgery units in the UK and Ireland. As part of an intergroup collaboration with the European Organisation for Research and Treatment of Cancer (EORTC) the trial will also open in 22 centres in mainland Europe. A feasibility survey completed by 10 UK centres provided information on the number of eligible patients and confirmed that the sample size is achievable.

### Neurocognitive function assessment

NCF will be assessed using a standard validated battery of tests to measure verbal and visual memory, executive skills, processing speed, language, working memory, mood and visuo-spatial construction. These are important parameters to assess and determine whether radiotherapy has any adverse impact on neurocognitive function in patients with meningioma. The following tests will be used: Hopkins Verbal Learning Test, REY Complex Figure Test, Dass21, Stroop Trail Making Test, Symbol Digit Modality Test, WAIS-IV (Digit Span and Blocks Test), Graded Naming Test and Benton Verbal Fluency Test. Additionally, consent will be sought for longer term follow up NCF assessment 5 years after surgery to assess the later effects of treatment in both the radiotherapy and observation arms.

### Patient and public involvement

The involvement of consumers has been fundamental to the design of this trial, and it is recognised that patients and carers have unique experience and expertise, which they can bring to this study. This enables them to be part of the solution to the problems faced by researchers when designing a trial. They have played an active role in the idea generation, trial design and funding application. Their voice will continue to play a significant role in the preparation and execution of this study and the dissemination of results.

### Study population

The trial will be open to all adult patients with atypical meningioma who meet the eligibility criteria.

### Inclusion criteria

For inclusion, each patient must meet the following criteria:Histologically confirmed newly diagnosed solitary atypical meningioma (WHO grade II) based on the 2007 WHO criteria [1]Age ≥ 16 yearsAll anatomical locations allowed except optic nerve sheath tumourComplete resection (Simpson 1, 2 or 3) as assessed by the surgeonAble to commence radiotherapy between within 12 weeks of surgery (ideally 8 to 12 weeks)WHO performance status 0, 1 or 2Women of reproductive potential must use effective contraception for the whole duration of the treatmentAbsence of any psychological, familial, sociological or geographical condition potentially hampering compliance with the study protocol and follow-up schedule; those conditions should be discussed with the patient before registration in the trial.

### Exclusion criteria

Patients exhibiting any of the following will be excluded from the study:Neurofibromatosis type II (NF-2)Optic nerve sheath tumoursMultiple meningiomasRadiation induced meningiomaClinical evidence of second malignancies, except a history of cervix carcinoma in situ and/or basal cell carcinomaPrevious intracranial tumourPregnant or lactating women.

### Primary endpoint

The primary endpoint will be the time to MRI evidence of tumour recurrence or death due to any cause (disease-free survival (DFS))

### Secondary endpoints

The secondary endpoints will include the following:Toxicity assessed by CTCAE (Common Terminology Criteria for Adverse Events)Quality of lifeNeurocognitive functionTime to second-line (salvage) treatment (surgery, radiotherapy, and radiosurgery)Time to death (overall survival (OS))Health economic analysis (incremental cost per QALY gained)

**Disease-free survival (DFS)** will be counted from the date of surgery until the date of MRI evidence of tumour recurrence or death due to any cause. Only clear dural thickening at the distinction of the investigator is to be considered tumour.

**Overall survival (OS)** will be counted from the date of surgery until death due to any cause.

### Randomisation

Patients will be randomised to early radiotherapy or observation in a ratio of 1:1. Written informed consent will be obtained following surgical resection and histopathological confirmation of an atypical meningioma.

### Proposed sample size

Atypical meningioma 5-year tumour recurrence rates are reported as between 39 and 58 %. A 0.05 level two-sided log-rank test for equality of survival curves with 80 % power would require 86 patients in each arm (total number of events required = 46) to detect an absolute reduction from 40 % in the control group arm to 20 %. A strong magnitude of effect is required to impact clinical practice and establish a treatment policy across the NHS in the UK. This is due in part to the expense of radiotherapy but also the burden to patients - due to the side effects of radiotherapy (hair loss, skin irritation, cognitive decline, and secondary malignancy) and its delivery requiring patients to attend the hospital daily (Monday through Friday) for 6 weeks. Patient retention will be high as patients with atypical meningioma are routinely followed up for the long term, and data will be collected at routine clinic visits. However, an adjustment to allow for a 10 % loss to follow-up has been made, requiring a total of 190 patients to be recruited. This sample size calculation has been agreed upon with the EORTC. The UK arm of the trial will aim to deliver 118 participants with a total of 29 events providing 60 % power. The remaining participants would be recruited across Europe within the EORTC intergroup collaboration.

### Statistical analysis

The trial will be analysed and reported using the ‘Consolidated Standard of Reporting Trials’ (CONSORT) and the International Conference on Harmonisation E9 guidelines. A full and detailed statistical analysis plan will be developed prior to the final analysis of the trial. The main features of the statistical analysis plan are included here.

The primary analysis will be by intention-to-treat principle, as far as is practically possible. Results will be presented throughout using 95 % confidence intervals and a 5 % level of statistical significance. Time to event outcomes will be analysed using Kaplan Meier curves, log rank tests and Cox Proportional Hazards models. Assumptions of proportional hazards will be investigated. Ordinal categorical outcomes will be analysed using an ordinal logistic model. Continuous outcomes will be assessed using ANCOVA methods.

